#### Data Analysis Plan for Aim 3: Predicting Between-Group Treatment Outcomes

Assuming that the models from the previous aim have levels of prediction accuracy, each of the within-group models will be used to generate predicted outcomes for each couple’s likelihood of adhering to the program as well as their treatment gains, creating counterfactual estimates of program completion and treatment gains as if each couple in the data set completed each intensity and method of coach contact [14].

To do this, the within-group models built in aim 1 will be used to generate potential outcomes for each couple’s likelihood of adhering as well as their gains in a (1) full coaching, (2) automated coaching, and (3) contingent coach conditions. If, in aim 1, the interaction terms result in a better RMSE, models will be constructed based on treatment assignment (ie, OurRelationship or ePREP) and coach assignment (ie, full, contingent, or automated). The estimates between the conditions for each couple’s between-group treatment differences between the full and automated coaching conditions can be understood as:

where 
[figure not shown]
 is the between-group likelihood of treatment adherence or gains for couple x, *Ŷ*(*x, Full Coach*) is the within-group likelihood of treatment adherence or gains for couple x in the full-coach condition, and *Ŷ*(*x, Contingent Coach*) is the within-group likelihood of treatment adherence or gains for couple x in the contingent coach condition [14]. These hypothetical between-group outcomes will then serve as dependent variables in a second random forest to calculate VIMP, which will identify the most powerful predictors of between-group differences. After identifying the most powerful predictors using VIMP, a multiple regression model will be estimated using the reduced set of variables to aid in the interpretation of the main effects. This process will thereby help clinicians determine which couples should be assigned to which level of coach contact.

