### This Study: Research Aims and Hypotheses

Given past research, this study has 3 aims. The first aim is to investigate how well we can predict the completion rates and changes in relationship satisfaction. As model evaluation has rarely been used in this area of research, no specific hypotheses have been posited. The second aim of this study is to document the most powerful predictors of treatment adherence and gains in relationship satisfaction within 3 different levels of coaching. More specifically, what are the most powerful predictors of treatment adherence and gains in relationship satisfaction in a full-coach condition (with 4 scheduled 15-minute phone calls), automated coach condition (where couples only receive emails), and a contingent coach condition (where couples only receive scheduled coach calls after displaying a pattern of nonadherence)? Although many of the findings in this area of research are inconclusive, 2 findings are relatively consistent: lower external stress and higher intrinsic motivation both predict treatment adherence and gains. Thus, we hypothesize that, regardless of coach assignment, lower external stress and higher intrinsic motivation will emerge as reliable predictors of better adherence to the web-based program and subsequent treatment gains. In the final aim of the study, we intend to use the information gathered in the first 2 steps to determine the most powerful predictors of between-group differences. More specifically, what baseline characteristics are indicative of a given couple’s adherence or gains in relationship satisfaction to couples assigned to the full-coach program compared with automated coaching, contingent coaching, or the waitlist control condition? As this area of research is relatively underdeveloped, no specific hypotheses will be posited.

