## Methods

### Procedure

This study was funded by the US Department of Health and Human Services, ACF (grant number 90PD0309; see Multimedia Appendix 1 for peer reviews). The parent study was registered with ClinicalTrials.gov (NCT02806635). The analyses and project design for this study will be preregistered with the Open Science Framework to promote accountability. Data for this study come from a large (N=1248 couples; N=2496 individuals) web-based RCT with a Sequential Multiple Assignment Randomized Trial design [44]. Sequential Multiple Assignment Randomized Trial designs are experiments that allow researchers to develop adaptive interventions and reassign nonadherent participants [44]. This was done by varying the levels and types of coach contact that a couple receives. In this study, couples were initially assigned to one of five conditions: OurRelationship coach, OurRelationship automated (email only), ePREP coach, ePREP automated (email only), and the waitlist control condition. However, couples initially assigned to the no-coach condition that did not complete scheduled web-based activities for >2 weeks underwent a second randomization: to continue the program without a coach or to be assigned to a coach for the remainder of the program. Those who were randomized to continue without a coach were still allowed to access the program, complete the activities, and were still sent automated reminders. In contrast, those who were randomly reassigned to receive coach contact were emailed by a coach and invited to schedule a call. Couples in this contingent coach condition received up to 3 additional calls (for a maximum of 4 calls) depending on where in the program they were when they stopped making adequate progress. This full variability of possible coaching contact, all of which involved random assignment, will allow us to determine the most powerful predictors of which couples should receive 4 15-minute coach calls, those who should simply receive emails, and those who should receive contingent coach contact after displaying patterns of treatment nonadherence.

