### Participants

A total of 226 couples were randomly assigned to the OurRelationship coach condition, 145 couples were assigned to the OurRelationship contingent coach condition, and 145 couples were assigned to the OurRelationship automated (ie, email only) condition. Similarly, 222 couples were assigned to the ePREP coach condition, 143 couples were assigned to the ePREP contingent coach condition, and 143 couples were assigned to the ePREP automated (ie, email only) condition. A total of 224 couples were assigned to the waitlist control condition. In total, 4 individuals from the OurRelationship coach condition, 2 from the OurRelationship contingent coach condition, and 2 from the OurRelationship automated condition asked to discontinue and have their data removed from the study. Furthermore, 3 individuals from the ePREP coach condition, 2 from the ePREP contingent coach condition, and 3 from the ePREP automated condition asked to discontinue and have their data removed from the study.

In total, 47.5% (1178/2480) of the sample identified as male, and 52.5% (1302/2480) of the sample identified as female. The average length of the relationship was 5.74 years (SD 5.18). Most of the participants reported belonging to an opposite-gender relationship (2318/2480, 93.47%), and a smaller percentage were in same-gender relationships (162/2480, 6.53%). Most participants identified as White non-Hispanic (1520/2480, 61.29%), fewer identified as Black (434/2480, 17.5%), White Hispanic (279/2480, 11.25%), Black Hispanic (28/2480, 1.13%), American Indian or Alaskan Native (23/2480, 0.93%), Asian (17/2480, 0.69%), Hawaiian or Pacific Islander (4/2480, 0.16%), and Biracial (86/2480; 3.47%); and 3.59% (89/2480) of participants belonged to a race that was not listed. Furthermore, 6.81% (169/2480) of participants did not have a degree or diploma, 12.3% (305/2480) had earned a general education diploma, 14.23% (353/2480) had completed high school, 8.23% (204/2480) had a technical or vocational certification, 22.54% (559/2480) had some college degree, 8.83% (219/2480) had graduated with an associate’s degree, 10.69% (265/2480) had a bachelor’s degree, and 2.38% (59/2480) had a master’s or advanced degree.

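### Aim 3 names the waitlist as a comparator, but no waitlist model is planned, and the one contrast written out has a label and a second term that disagree

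*Protocol article*

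**What the plan says.** All references are to the Protocol article.

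- **This Study: Research Aims and Hypotheses.** Aim 3 asks which baseline characteristics go with completion or satisfaction gain in "couples assigned to the full-coach program compared with automated coaching, contingent coaching, or the waitlist control condition".
- **Procedure and Participants.** The waitlist is one of the five initial randomised conditions; the list ends with "ePREP automated (email only), and the waitlist control condition". Its size is given: "A total of 224 couples were assigned to the waitlist control condition". The total is also given: "Data for this study come from a large (N=1248 couples; N=2496 individuals) web-based RCT".
- **Data Analysis Plan for Aim 1.** Depending on a test of program interactions, there will be three models (full, contingent, automated) or six (each program by each coaching level). All are named, and none is a waitlist model.
- **Data Analysis Plan for Aim 2.** The same three coaching levels are listed, or the six cells if the programs are kept apart.
- **Data Analysis Plan for Aim 3.** The Aim 1 models supply each couple's predicted completion and their "gains in a (1) full coaching, (2) automated coaching, and (3) contingent coach conditions". One contrast is written out. The lead-in says the "between-group treatment differences between the full and automated coaching conditions can be understood as" the equation that follows, but the clause defining its terms says the second one "is the within-group likelihood of treatment adherence or gains for couple x in the contingent coach condition". The equation itself is missing from the text available here.
- **Baseline Measures of Relationship and Individual Symptomology.** Baseline satisfaction is itself among the candidate predictors.

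**The concern.** Three separate things are at stake.

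1. A stated research question has no analysis behind it. Full coaching minus waitlist needs a prediction under the waitlist condition, and no listed model can supply one. This is more than detail left to a fuller plan, because the article gives closed lists of models that do not cover its own aim.
2. The one contrast written out becomes the dependent variable of the second forest, whose output is meant to guide which couples get which level of coaching. If its label and its terms differ, the results can be reported against the wrong comparison.
3. Within an arm, change in satisfaction mixes program effect with natural change and regression to the mean. A baseline factor can then predict the change without predicting any benefit from the program. The waitlist is the only arm that could separate the two.

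**Working it through.** **Step 1. Reproduce the allocation (Participants).**

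- OurRelationship: 226 + 145 + 145 = 516
- ePREP: 222 + 143 + 143 = 508
- Waitlist: 224
- Total: 516 + 508 + 224 = 1248 couples, or 2 × 1248 = 2496 individuals, as stated. Removing the 4 + 2 + 2 + 3 + 2 + 3 = 16 withdrawn individuals gives 2480, the denominator the article uses.

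**Step 2. Who trains a model.**

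- Full: 226 + 222 = 448
- Contingent: 145 + 143 = 288
- Automated: 145 + 143 = 288
- Sum: 1024
- Remainder: 1248 − 1024 = 224 waitlist couples; 224/1248 = 17.9%

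**Step 3. Contrasts asked for against contrasts available.**

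| Contrast | Named in the aims | Both models listed |
|---|---|---|
| Full − automated | yes | yes |
| Full − contingent | yes | yes |
| Full − waitlist | yes | no waitlist model |

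For the contrast written out, the lead-in gives full and automated, and the definitions give full and contingent. Both are intended comparisons, so the text does not show which side is the slip.

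**Step 4. Regression to the mean in within-arm gain.** Assume that gain is the raw change Y1 − Y0, that baseline and follow-up have equal variance σ², and that their correlation is ρ. The article gives none of these.

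- Cov(Y1 − Y0, Y0) = −σ²(1 − ρ)
- Var(Y1 − Y0) = 2σ²(1 − ρ)
- Correlation of gain with baseline = −√((1 − ρ)/2), so R² = (1 − ρ)/2, and the slope is −(1 − ρ)

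| ρ (assumed) | Correlation | R² | Slope |
|---|---|---|---|
| 0.5 | −0.50 | 0.25 | −0.50 |
| 0.6 | −0.45 | 0.20 | −0.40 |
| 0.7 | −0.39 | 0.15 | −0.30 |
| 0.8 | −0.32 | 0.10 | −0.20 |

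A constant program effect shifts every gain equally and leaves this table unchanged. Simulation with 200,000 couples per arm and a constant effect of 0.5 SD agrees. At ρ = 0.5 the slope is −0.501 in the treated arm and −0.498 on the waitlist; at ρ = 0.8 it is −0.202 and −0.200. The difference in slopes is about zero throughout, as it should be when no factor modifies the effect.

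**Step 5. Is the waitlist large enough to be worth modelling?** Assume two-sided α = 0.05, 80% power, and d in SD units of the couple average. The smallest detectable average difference is (1.960 + 0.842) × √(1/n + 1/224).

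- n = 448 (full): 2.802 × 0.0818 = 0.23
- n = 288 (contingent or automated): 2.802 × 0.0891 = 0.25

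The Introduction cites satisfaction effects against a waitlist of d = 0.53 and 0.42 in an earlier trial of these programs. At those sizes power would exceed 99%; at d = 0.20 it would be 69% (n = 448) or 61% (n = 288). These figures concern average effects. They say nothing about power to find moderators.

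**The case against.** The strongest reply is that the waitlist is a stray phrase. The abstract's objective compares predictors among three levels of coach contact only, the Procedure states the purpose as choosing among calls, emails and contingent contact, and the Aim 3 plan ends on the level of coach contact. Completion is defined by the program assigned, so it has no meaning on the waitlist. Deleting the waitlist from the aim would remove the contradiction. That stands, and it is offered below as an alternative remedy. It does not make the present text consistent.

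Four stronger readings are tempting but unsupported.

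- *The 224 couples are wholly unused.* The Aim 3 plan generates predictions for every couple in the data set, so waitlist baseline data could be scored and enter the second forest. Only their outcomes train nothing.
- *Natural change biases the Aim 3 coaching contrasts.* In a difference between randomised coaching arms it cancels in expectation. It affects Aims 1 and 2 and each predicted gain taken singly.
- *Baseline satisfaction, breakup potential, conflict and support will rank at the top in every arm.* The calculation covers baseline satisfaction only and rests on assumed correlations. Nothing shows how its correlates would rank with baseline satisfaction in the same forest.
- *The formula computes the wrong contrast.* The equation cannot be seen, and full versus contingent is itself wanted. Only the mismatch in the surrounding text is established.

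It is also fair to say that Aims 1 and 2 are openly within-group, and that predicting change within an arm needs no control. The question can stay as it is; what needs care is describing that change as treatment gain.

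**Conclusion.** The point holds as an internal inconsistency that should be fixed. Two parts rest on the text alone: the waitlist comparison named in Aim 3 cannot be computed from the models listed, leaving the outcomes of 224 of 1248 couples (17.9%) without a model; and the single contrast disagrees with its own label.

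The third part is conditional. If gain is a raw change score, variances are equal, and the pre-post correlation lies between 0.5 and 0.8, baseline satisfaction would explain about 25% to 10% of within-arm gain with no program effect. This calls for careful wording in Aims 1 and 2; it does not undermine the coach-versus-coach contrasts.

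**What to change.** If the waitlist comparison is intended:

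- fit one more within-group forest on the waitlist couples, for satisfaction only;
- add each coaching level minus waitlist to the Aim 3 contrasts for satisfaction;
- reserve the term *predictor of treatment gain* for factors that predict that difference.

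If it is not intended, remove the waitlist from the statement of Aim 3.

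In either case:

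- make the label and the terms of the Aim 3 contrast agree, and write out every pairwise contrast to be analysed;
- describe Aim 2 results as predictors of pre-post change within an arm.

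The cost is at most one additional model and its contrasts on data already collected; otherwise it is wording. There is still time to prespecify this: the Results section says only completion rates have been analysed, and the Procedure section describes the preregistration as still to come.

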#### Data Analysis Plan for Aim 2: What Are the Most Important Within-Group Predictors?

The second research question is: what are the most powerful predictors of treatment adherence and gains in relationship satisfaction within (1) the full-coach condition, (2) the automated coach condition, and (3) the contingent coach condition? If, in aim 1, the interaction terms result in a lower RMSE, better sensitivity, or better specificity, models will be constructed based on treatment assignment (ie, OurRelationship or ePREP) and coach assignment (ie, full, contingent, or automated). One statistically powerful way to test the most potent predictors of treatment adherence and gains is through the use of variable importance (VIMP). VIMP is a nonparametric approach within the random forest algorithm, which can help investigators identify which variables play a key role in predicting a binary (eg, program completion) or continuous (eg, improvements in relationship satisfaction) variable [53]. VIMP has been calculated in many ways in the past; however, one way that has shown promise has been through permutation (ie, Briemen–Cutler) importance [53]. This method randomly changes a given variable’s out-of-bag data and compares and averages the permuted prediction error with the original error resulting in VIMP [53]. This process not only helps identify which variables play a key role in prediction but also overcomes issues of overtesting using bootstrapping. Recent studies have used these out-of-bag estimates to generate CIs to test whether a variable has a meaningful effect in predicting an outcome with great success [53]. Indeed, these studies have suggested that 95% CIs that do not include zero will be assumed to have reliable predictors [53]. After identifying the most powerful predictors using VIMP, a multiple regression model will be estimated using the reduced set of variables to aid in the interpretation of the main effects, helping clinicians identify predictors of treatment adherence and gains.

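### Aim 3 treats the difference between two forest predictions as observed data, so its VIMP and regression results do not measure whether the coaching effect differs between couples

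*Protocol article*

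**What the plan says.** The Aim 3 section of the Protocol article sets out the sequence:

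- **First stage.** "the within-group models built in aim 1 will be used to generate potential outcomes for each couple’s likelihood of adhering", and likewise their gains, under full, automated and contingent coaching. This is done for all couples, "creating counterfactual estimates of program completion and treatment gains as if each couple in the data set completed each intensity and method of coach contact".
- **Second stage.** Predictions are subtracted between conditions. "These hypothetical between-group outcomes will then serve as dependent variables in a second random forest to calculate VIMP".
- **Regression.** After VIMP, "a multiple regression model will be estimated using the reduced set of variables to aid in the interpretation of the main effects".
- **Use.** "This process will thereby help clinicians determine which couples should be assigned to which level of coach contact".

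The section makes this conditional on the earlier models having some predictive accuracy. It gives no threshold and no test that coaching effects vary.

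The rule for calling a predictor reliable is in the Aim 2 section: "95% CIs that do not include zero will be assumed to have reliable predictors". That section also says of permutation VIMP that it "overcomes issues of overtesting using bootstrapping". The Aim 3 section does not restate the interval rule. It says only that VIMP will identify the strongest predictors of between-group differences.

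**The concern.** The choice of dependent variable is the problem, and the article fixes that choice itself. A predicted difference contains whatever each forest picked up by chance in its own arm, and those chance patterns are patterns in the baseline predictors. A second forest or a regression on the same predictors will find them again and present them as moderation. Resampling at the second stage cannot reveal this, because it never refits the first stage.

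Aim 3 is the step meant to guide which couples receive which level of coaching. Little or no moderation is a realistic possibility here. The article's own review (The Effect of Having a Coach on Program Outcomes) reports that 2 of 20 baseline moderators interacted with coaching level in the OurRelationship program, and that a study of stress and anxiety interventions found none. A method that returns a long list of moderators when none exist cannot improve on that evidence.

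**Working it through.** The article states no error rate for Aim 3, so there is no figure to reproduce.

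**Algebra.** Let m_F(x) and m_A(x) be the true mean outcomes under full and automated coaching for a couple with baseline values x, and e_F(x) and e_A(x) the estimation errors of the two forests. The dependent variable is

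D(x) = [m_F(x) + e_F(x)] − [m_A(x) + e_A(x)].

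With no moderation, m_F(x) − m_A(x) = c, so D(x) = c + e_F(x) − e_A(x). All variation in D is forest error, and it is a function of x. Out-of-bag prediction for a couple's own arm changes only which trees are averaged.

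**Inputs from the article.**
- Full coach: 226 + 222 = 448 couples. Automated: 145 + 143 = 288. Contingent: 145 + 143 = 288. The symbols under the Aim 3 formula name the contingent arm where the lead-in names the automated arm; both have 288 couples, so the sizes are the same either way.
- Candidate predictors, counted from the Measures sections: 6 demographic + 7 relationship (including baseline satisfaction) + 4 stress and health + 2 motivation = 19.

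**Assumptions not in the article.** Predictor correlation 0.2; four binary predictors; 200 trees, 7 variables tried per split, leaf size 5. Outcomes depend on the predictors identically in every arm: a continuous outcome with prognostic R² 0.20, and a binary one with about 60% completion. VIMP intervals come from subsampling, with subsample size 32 (20 runs per setting) or 256 (8 runs). D is computed for all 448 + 288 + 288 = 1024 couples.

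**Share of the 19 predictors flagged when nothing moderates the effect:**

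| Outcome, own-arm prediction | VIMP interval excludes 0 (32 / 256) | p<0.05 in regression after selection (32 / 256) | p<0.05 in regression on all 19 (60 runs) |
|---|---|---|---|
| Continuous, in-sample | 64% / 42% | 38% / 30% | 47.5% |
| Continuous, out-of-bag | 59% / 43% | 44% / 34% | 56.4% |
| Binary, in-sample | 69% / 55% | 48% / 39% | 48.9% |
| Binary, out-of-bag | 64% / 51% | 51% / 43% | 59.6% |

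As counts, VIMP flags from 0.42 × 19 = 8 to 0.69 × 19 = 13 predictors. The nominal expectation is 0.05 × 19 = 0.95.

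**Spurious signal.** D had an SD of 0.27-0.40 on the continuous outcome and 0.13-0.20 in completion probability, although the true difference was constant. The second forest explained D with out-of-bag R² of 0.31-0.51.

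**Comparison on observed outcomes.** Predictor-by-coaching interaction tests on the 448 + 288 = 736 couples gave p<0.05 for 4.8% (continuous) and 3.4% (binary) of predictors over 60 runs.

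**Isolating the cause.** Among the 15 predictors given no effect, the VIMP rule applied to observed outcomes selected 6-8% (subsample 32) or 0% (256). Applied to D, it selected 50-62% or 28-46%. The excess comes from using predicted differences as data.

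**Other simulations.** A separate simulation (correlation 0.3, 12 replicates, D for 736 couples, equal prognostic effects) gave 39% in-sample and 51% out-of-bag by regression, 64-67% by VIMP, and 2-3% for interaction tests. A further null simulation at 448 and 288 couples gave 46% by regression and 7% for interaction tests.

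**The case against.** Several counter-arguments have force.

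- **The interval rule belongs to Aim 2.** Aim 3 can be read as a ranking, and its regression is described as an aid to interpretation with no p-value rule. This stands, and the VIMP shares apply only if the rule carries over. It does not rescue the step: with no moderation the ranking is of noise, and the regression on predicted differences still has standard errors that ignore first-stage error.
- **A reader might infer that most predictors will be called reliable moderators.** The documents and figures do not support that. Some VIMP settings and most of the regression results fall below half.
- **The accuracy condition.** Scenarios in which no predictor relates to outcome give still higher shares, but such models should fail any accuracy check, so they are not used here. Models that are prognostic in every arm can pass it with no moderation.
- **Predicting for couples used in training.** A reader might take this as the cause. The figures do not show it: in every row pair of the table, regression flagged more with out-of-bag predictions than in-sample.
- **Multiplicity.** Applied to observed outcomes, the Aim 2 rule was near nominal or conservative per predictor. The number of Aim 3 intervals cannot be fixed, because the article does not settle which contrasts will be run. What remains is narrow: bootstrapping yields an interval for each predictor and does not control error across them.
- **Unseen sources and exploratory status.** The article cites methods papers that are not at hand, promises preregistration, and posits no hypothesis for Aim 3. The dependent variable is nonetheless stated plainly, and the result is meant to inform assignment.

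**Conclusion.** The point holds in this form: second-stage VIMP and regression on predicted differences are not evidence of effect modification. With prognostic predictors and no moderation, roughly 40-70% of predictors are flagged by VIMP intervals (if the Aim 2 rule is carried over) and 30-60% by regression at p<0.05, against about 5% for interaction tests on observed outcomes. The mechanism follows from the algebra and does not depend on simulation settings. The percentages do: they rest on assumed correlations, forest settings and interval construction, with few runs for the VIMP part, and should be read as ranges. As planned, Aim 3 should not guide the assignment of couples to coaching levels.

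**What to change.** 1. Keep the within-group forests and the second forest, labelled as exploratory ranking.
2. Base any claim that a predictor moderates the coaching effect on observed outcomes, by one of two routes:
   - a regression of the observed outcome on coaching, predictors and coaching-by-predictor interactions, entering all candidates (as in the check above) and not only those picked from predicted differences; or
   - a regression of a cross-fitted doubly robust pseudo-outcome that uses the trial's randomisation probabilities. The article does not give these, and contingent coaching arises from a second randomisation of couples who fell behind, so they must be taken from the trial's design.
3. Alternatively, judge VIMP against a null that re-runs everything (imputation, within-group forests, differences, second forest) with coaching labels permuted after the average arm difference is removed. Permuting raw labels would test no coaching effect at all, not a constant effect. This route was not simulated here.
4. Replace the final regression on predicted differences with the analysis chosen in step 2 or 3.
5. Delete the Aim 2 statement that bootstrapping overcomes overtesting.

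Out-of-bag prediction alone is not sufficient.

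The cost is code, computing time and wording in the preregistration, which the article describes as still to come; it reports that only completion rates had been analysed. No new data are needed. The downsides are that fewer predictors will be declared and that linear interaction tests may miss nonlinear moderation.
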